##### 9.4.3.2 Relationship to Study Intervention/Experimental Manipulation

All adverse events (AEs) will have their relationship to study procedures, including the intervention, assessed by an appropriately trained clinician based on temporal relationship and his/her clinical judgment. The degree of certainty about causality will be graded using the categories below.

**Related** – The AE is known to occur with the study procedures, there is a reasonable possibility that the study procedures caused the AE, or there is a temporal relationship between the study procedures and the event. Reasonable possibility means that there is evidence to suggest a causal relationship between the study procedures and the AE.

**Not Related** – There is not a reasonable possibility that the study procedures caused the event, there is no temporal relationship between the study procedures and event onset, or an alternate etiology has been established.

*OR*

**Definitely Related** – There is clear evidence to suggest a causal relationship, and other possible contributing factors can be ruled out. The clinical event, including an abnormal laboratory test result, occurs in a plausible time relationship to study procedures administration and cannot be explained by concurrent disease or other drugs or chemicals. The response to withdrawal of the study procedures should be clinically plausible. The event must be pharmacologically or phenomenologically definitive.

**Probably Related** – There is evidence to suggest a causal relationship, and the influence of other factors is unlikely. The clinical event, including an abnormal laboratory test result, occurs within a reasonable time after administration of the study procedures, is unlikely to be attributed to concurrent disease or other drugs or chemicals, and follows a clinically reasonable response on withdrawal.

**Potentially Related** – There is some evidence to suggest a causal relationship (e.g., the event occurred within a reasonable time after administration of study procedures). However, other factors may have contributed to the event (e.g., the participant’s clinical condition, other concomitant events). Although an AE may rate only as “possibly related” soon after discovery, it can be flagged as requiring more information and later be upgraded to “probably related” or “definitely related”, as appropriate.

**Unlikely to be related** – A clinical event, including an abnormal laboratory test result, whose temporal relationship to study procedures administration makes a causal relationship improbable (e.g., the event did not occur within a reasonable time after administration of the study procedures) and in which other drugs or chemicals or underlying disease provides plausible explanations (e.g., the participant’s clinical condition, other concomitant treatments).

**Not Related** – The AE is completely independent of study procedures administration, and/or evidence exists that the event is definitely related to another etiology. There must be an alternative, definitive etiology documented by the clinician.

##### 9.4.3.3 Expectedness

A clinician with appropriate expertise in primary care will be responsible for determining whether an adverse event (AE) is expected or unexpected. An AE will be considered unexpected if the nature, severity, or frequency of the event is not consistent with the risk information previously described for the study procedures.

#### 9.4.4 Time Period and Frequency for Event Assessment and Follow-Up

While unlikely, the occurrence of an adverse event (AE) or serious adverse event (SAE) may come to the attention of study personnel during interviews of a study participant.

All AEs, not otherwise precluded per the protocol, will be captured on the appropriate case report form (CRF). Information to be collected includes event description, time of onset, clinician’s assessment of severity, relationship to study procedures (assessed only by those with the training and authority to make a diagnosis), and time of resolution/stabilization of the event. All AEs occurring while on study will be documented appropriately regardless of relationship. All AEs will be followed to adequate resolution.

Any medical or psychiatric condition that is present at the time that the participant is screened will be considered as baseline and not reported as an AE. However, if the study participant’s condition deteriorates at any time during the study, it will be recorded as an AE.

Changes in the severity of an AE will be documented to allow an assessment of the duration of the event at each level of severity to be performed. Documentation of onset and duration of each episode will be maintained for AEs characterized as intermittent.

The Project Coordinator and/or research associate will record all reportable events that occur during the one-time study participation for semi-structured interviews. Events will be followed for outcome information until resolution or stabilization.

#### 9.4.5 Adverse Event Reporting

Unexpected adverse events, serious adverse events, and other reportable events will be reported to the UCLA Institutional Review Board by the PI or the Project Coordinator. Decisions regarding relatedness and severity will be discussed among the investigative team.

An unanticipated problem that resulted in a subject’s death or was potentially life-threatening will be reported to the IRB within a shorter time frame than other unanticipated problems that were not life-threatening.  We will follow UCLA IRB guidelines in order to satisfy the requirement for *prompt* reporting:

1. Unanticipated problems that are serious adverse events will be reported to the UCLA IRB within 1 week of the investigator becoming aware of the event.
2. Any other unanticipated problem will be reported to the IRB within 2 weeks of the investigator becoming aware of the problem.
3. All unanticipated problems will be reported to appropriate institutional officials (as required by an institution’s written reporting procedures), the supporting agency head (or designee), and the UCLA Office of Human Research Protection within one month of the IRB’s receipt of the report of the problem from the investigator.

#### 9.4.6 Serious Adverse Event Reporting

In consultation with the PI, a trained member of the study team will be responsible for conducting an evaluation of a serious adverse event and shall report the results of such evaluation to the UCLA Institutional Review Board (IRB).

#### 9.4.7 Events of Special Interest

Not applicable

#### 9.4.8 Reporting of Pregnancy

Not applicable

### 9.5 Unanticipated Problems

#### 9.5.1 Definition of Unanticipated Problems (UP)

Any incident, experience, or outcome that meets **all** of the following criteria:

- Unexpected in terms of nature, severity, or frequency given (a) the research procedures that are described in the protocol-related documents, such as the Institutional Review Board (IRB)-approved research protocol and informed consent document; and (b) the characteristics of the participant population being studied; and
- Related or possibly related to participation in the research (“possibly related” means there is a reasonable possibility that the incident, experience, or outcome may have been caused by the procedures involved in the research); and
- Suggests that the research places participants or others (which many include research staff, family members or other individuals not directly participating in the research) at a greater risk of harm (including physical, psychological, economic, or social harm) than was previously known or expected.

#### 9.5.2 Unanticipated Problem Reporting

The investigator will report unanticipated problems (UPs) to the UCLA Institutional Review Board (IRB) according to the UCLA IRB’s policies.

## 10 STATISTICAL CONSIDERATIONS

### 10.1 Statistical Hypothesis

- ***Primary Endpoints***:

We hypothesize that the intervention (PT-AWV intervention) will result in:

- 1. greater AWV utilization (% of eligible patients completing an AWV or IPPE in the past 12 months) at 12, 18 and 24 months after intervention implementation
  2. patients being up to date on a greater percentage of their total number of recommended services (of a maximum of 12 recommended services per patient) at 12, 18 and 24 months after intervention implementation;

We also hypothesize that the PT-AWV intervention will reduce racial/ethnic disparities in AWV utilization. Alternatively, our null hypotheses are that there will be no difference in AWV or USPSTF and CDC/ACIP-recommended service utilization with implementation of the PT-AWV intervention and that there will be racial/ethnic disparities in AWV utilization.

- ***Secondary Endpoint***(s):

We hypothesize that the PT-AWV intervention will result in a greater percentage of patients who are up to date on each of the individual preventive health services listed in [Section 4.0](#_4_OBJECTIVES_AND) **Table 2**. Alternatively, our null hypothesis is that there will be no difference in utilization in the USPSTF and CDC/ACIP-recommended services examined.

### 10.2 Sample Size Determination

In our pilot practices, the PT-AWV intervention increased AWVs from 8% at baseline to 54% eight months post-intervention in AWV-eligible patients (n=213, 576 and 639 patients at baseline in the 3 practices). Practices agreeing to participate in this project range in size from about 175-2700 eligible patients and have baseline AWV rates of about 16-45%, with most patients belonging to practices with rates under 35%. At the population level, we conservatively estimate our sample size to be a mean of about 1300 patients per practice. Behaviors of practices recruited from the same healthcare organizations may be correlated, so we will adjust power analyses using intra-class correlation (ICC). Based on our preliminary data, intra-class correlation for site was 0.03 and within subject correlation was -0.003 for AWV use one year apart. Since the stepped wedge design is relatively insensitive to ICC (because it is similar to a pre-test/post-test design), we conservatively estimate ICCs from .03 to .05 in our calculations and assume that ICC is mostly due to repeated patients seen in the same practice. Clinically meaningful increases would conservatively be 10% for all outcomes. The overall treatment effect is >99% for a 10% increase in AWVs and in the composite preventive health services score, based on a type-I error rate α = 0.05, 800-1300 patients per practice, and ICC=0.03 and 0.05 for 24 practices.

**Table 4** demonstrates power calculations to detect a meaningful treatment effect of 10% increase outcomes for a sample of 24 practices, with type-I error rate α = 0.05. We have >99% power to detect an overall improvement of 10% in AWV completion rates and the composite preventive health score in all scenarios from baseline to 12 months post-intervention.

| **Table 4. Power for treatment effect of 10% increase, type-I error rate α = 0.05, based on # monthly eligible patients and baseline rates of outcomes, and ICC for 24 practices** | | | |
| --- | --- | --- | --- |
| **Outcome / Mean # patients per site** | **Baseline rate, %** | **Power with ICC 0.05, %** | **Power with ICC 0.03, %** |
| ***AWV*** |  |  |  |
| 800 patients / practice | 10 | >99 | >99 |
|  | 30 | >99 | >99 |
|  | 50 | >99 | >99 |
| 1200 patients / practice | 10 | >99 | >99 |
|  | 30 | >99 | >99 |
|  | 50 | >99 | >99 |
| 1500 patients / practice | 10 | >99 | >99 |
|  | 30 | >99 | >99 |
|  | 50 | >99 | >99 |
| ***Composite preventive health score*** |  | >99 | >99 |
| 800 patients / practice |  | >99 | >99 |
| 1200 patients / practice |  | >99 | >99 |
| 1500 patients / practice |  | >99 | >99 |

Our pilot data suggested a decrease in ***racial/ethnic disparities*** in AWV utilization: at baseline, 7.7% of White patients and 4.9% of non-Whites completed AWVs (p=0.09), whereas 6 months post-implementation, 49.8% of White patients and 50.5% of non-Whites completed AWVs (p=0.63).

**Table 5** demonstrates power calculations to detect a 5% reduction in racial/ethnic disparities for AWVs with a sample of 24 practices, ICC=0.05 and type-I error rate α = 0.05. We will have >99% power to detect a 5% reduction in racial/ethnic disparities in AWVs between White and Hispanic patients and >99% power to detect a 5% reduction in disparities between White and Black patients for AWV completion. This calculation assumes the intervention effect is about 10% for White patients and 15% for Black and Hispanic patients, and that about 60%, 20% and 15% of the study population are White, Hispanic, and Black. For the composite preventive health services score power calculation, we further assume that on average each patient is eligible for > 8 preventive health services.

| **Table 5. Power for detecting 5% reduction in racial/ethnic disparities for AWVs and composite preventive health services score, with a type-I error rate α = 0.05 and ICC=0.05, based on patients/practice and baseline rates of outcomes** | | | | |
| --- | --- | --- | --- | --- |
| **Outcome** | **Baseline rate, %** | **Baseline rate, %** | **Power for Black-White disparity reduction, %** | **Power for Hispanic-White disparity reduction, %** |
| ***AWV*** | ***White*** | ***Black/Hispanic*** |  |  |
| 800 patients / practice | 30 | 10 | >99% | >99% |
|  |  | 15 | >99% | >99% |
|  |  | 20 | >99% | >99% |
|  | 40 | 10 | >99% | >99% |
|  |  | 15 | >99% | >99% |
|  |  | 20 | >99% | >99% |
|  | 50 | 10 | >99% | >99% |
|  |  | 15 | >99% | >99% |
|  |  | 20 | >99% | >99% |
| 1200 patients / practice | 30 | 10 | >99% | >99% |
|  |  | 15 | >99% | >99% |
|  |  | 20 | >99% | >99% |
|  | 40 | 10 | >99% | >99% |
|  |  | 15 | >99% | >99% |
|  |  | 20 | >99% | >99% |
|  | 50 | 10 | >99% | >99% |
|  |  | 15 | >99% | >99% |
|  |  | 20 | >99% | >99% |
| 1500 patients / practice | 30 | 10 | >99% | >99% |
|  |  | 15 | >99% | >99% |
|  |  | 20 | >99% | >99% |
|  | 40 | 10 | >99% | >99% |
|  |  | 15 | >99% | >99% |
|  |  | 20 | >99% | >99% |
|  | 50 | 10 | >99% | >99% |
|  |  | 15 | >99% | >99% |
|  |  | 20 | >99% | >99% |
|  |  |  |  |  |
| ***Composite preventive health services score*** |  |  |  |  |
| 800 patients / practice | 40 | 10 | >99% | >99% |
|  |  | 15 | >99% | >99% |
|  |  | 20 | >99% | >99% |
| 1200 patients / practice | 40 | 10 | >99% | >99% |
|  |  | 15 | >99% | >99% |
|  |  | 20 | >99% | >99% |
| 1500 patients / practice | 40 | 10 | >99% | >99% |
|  |  | 15 | >99% | >99% |
|  |  | 20 | >99% | >99% |

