## 5 STUDY DESIGN

### 5.1 Overall Design

This is a multi-site, stepped wedge cluster randomized controlled trial to evaluate the effect of the PT-AWV intervention on AWV and preventive health services use. The study will take place in 24 primary care practices around the United States (8 community-based, 8 academic, and 8 safety net practices). Recruitment and intervention implementation occur at the practice level. We hypothesize that the intervention will increase uptake of AWVs and use of preventive health services.

The **stepped wedge cluster design** is a pragmatic study design that includes an initial control period in which no clusters receive the intervention. Randomized clusters cross to the intervention condition at regular intervals, and there is a period at the end of the study where all clusters have been exposed to the intervention. Data are collected throughout the study so that each cluster contributes to both the control and intervention periods.[^155-157^](#_ENREF_155) The intervention will be implemented sequentially over 15 months, with 4 clusters of 6 practices each switching from control to intervention every 3 months. For each practice, intervention implementation will occur over a 6-month period. All practices will complete intervention implementation 15 months after the onset of intervention implementation in the first set of practices.

Outcomes for the primary and secondary endpoints will be assessed through EHR data extractions. The DARTNet Institute (co-investigator [name], PhD) will serve as the data coordinating center for the study. Co-investigator [name] at the American Academy of Family Physicians National Research Network (AAFP NRN) will clean, de-identify and create flags to develop analytic datasets. The AAFP NRN has established contracts and agreements with the DARTNet Institute that enable [name] to access DARTNet’s data. [name] will deliver limited datasets to investigators at the University of California, Los Angeles for analyses.

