### 5.3 Justification for Intervention

**Intervention Pilot-Testing.** The investigators successfully pilot-tested the PT-AWV intervention in an organization consisting of 3 practice sites.[^158^](#_ENREF_158) All practices used the eMDs EHR platform. As shown in **Figure 2**, AWV utilization in the past 12 months (across all sites) went from 7% at baseline to 54% eight months post-intervention implementation. Two larger practices each increased AWVs by about 40%, while the smallest practice doubled its AWVs (from 15% to 30%) before dropping to 21%.

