### 7.2 Fidelity

#### 7.2.1 Interventionist Training and Tracking

Variability of intervention implementation is expected because the intervention will be tailored by site. We will track dates of completion of meetings and trainings.

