#### 10.4.2 Analysis of the Primary Endpoints

The primary endpoints are AWV utilization and the composite preventive health services score **(Table 6)**.

| **Table 6. Patient cohorts, primary endpoints, and timing of measurement** | | |
| --- | --- | --- |
| **Cohort** | **Endpoints** | **Time Frame** |
| Medicare patients aged 50+, with 1 or more visits in the past 12 months, not deceased | 1) ***AWV utilization*** (% of patients who completed an AWV or IPPE (CPT codes G0438, G0439, G0402)) within 12 months; 2) ***Composite preventive health services score*** (% of recommended services that are up to date) | Monthly |

***Primary objectives (examine effect of PT-AWV intervention on increasing AWVs and preventive health services utilization in diverse practice settings at 12, 18 and 24 months post-implementation)*:** we will use **linear mixed effects models** to assess the effect of the intervention on the use of AWVs and on the composite preventive health services score. These models account for correlation between repeated observations in the same cluster and the confounding effects of time and treatment. For example, with $Y_{ijt}$ as the indicator of AWV completion for patient i from cluster j at time t, the model is:

$Y_{ijt}=\mu+\alpha_{i}+\gamma_{j}{+ \beta}_{t}+X_{ijt}\theta+ Z_{ijt} + \varepsilon_{ijt}$,

where $\mu$ is the intercept,$\gamma_{i}$ and $\alpha_{j}$ are the random intercepts for subject i and cluster j with $\alpha_{j}\sim N\left( 0, \sigma_{\alpha}^{2} \right), \gamma_{j}\sim N\left( 0, \sigma_{\gamma}^{2} \right),$ $\beta_{t}$ is the fixed time effect, $X_{ijt}$ is the indicator of treatment mode for subject i cluster j at month t, $\theta$ represents the treatment effect, $Z_{ijt}$ is pre-specified patient and practice level covariate, and $\varepsilon_{ijt}$ is the residual with $\varepsilon_{ijt}\sim N\left( 0, \sigma_{\varepsilon}^{2} \right)$. We will approximate the secular time trend $\beta_{t}$ linearly in time with $\beta t$. Piece-wise constant time effect will be considered to accommodate possible non-linear time trends. This model will accommodate repeated patient visits and correlations within practices. All analyses will be carried out based on the intention to treat principle, which means that the treatment mode variable ($X_{ijt})$ is determined by the scheduled assignment of intervention implementation based on randomization, but not by the actual timing of implementation.

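### The primary model gives every practice the same treatment effect, so its confidence interval is too narrow if gains differ between practices; the >99% power rests on the same unstated assumption

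*Protocol*

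**What the plan says.** **Power (Protocol 10.2).** The effect size is one value: "Clinically meaningful increases would conservatively be 10% for all outcomes". The text reports power above 99% "based on a type-I error rate α = 0.05, 800-1300 patients per practice, and ICC=0.03 and 0.05 for 24 practices", and then: "We have >99% power to detect an overall improvement of 10% in AWV completion rates and the composite preventive health score in all scenarios". The title of Table 4 lists what is varied: "based on # monthly eligible patients and baseline rates of outcomes, and ICC for 24 practices". No between-practice spread of the effect is among these inputs.

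**Model (Protocol 10.4.2).** The displayed linear mixed model has random intercepts for subject and cluster, a time effect, covariates and one coefficient θ, which "represents the treatment effect". The section then lets θ vary randomly over time since the intervention. It does not let θ vary over practices.

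**Variation between practices.** Section 5.3 reports on the pilot: "Two larger practices each increased AWVs by about 40%, while the smallest practice doubled its AWVs (from 15% to 30%) before dropping to 21" per cent. Section 7.2.1 says: "Variability of intervention implementation is expected because the intervention will be tailored by site". The footnote to Table 3 in 7.1.1 leaves each practice free to choose its tools and makes none of them compulsory.

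**The concern.** A random intercept covers stable differences in level between practices. In a stepped wedge these largely cancel, because each practice is compared with itself; 10.2 makes this point when it calls the design fairly insensitive to the ICC. Differences in the size of the gain do not cancel. They enter the estimated effect directly, and adding patients does not reduce them.

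A model with one θ for all practices treats that variation as absent. Its standard error then reflects mainly patient-level sampling. What is at stake is the reported interval for the primary endpoints: it would look far more precise than 24 differently responding practices can justify, in a trial whose intervention is meant for wide dissemination (7.1.1). The power statement carries the same assumption without saying so.

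**Working it through.** **Inputs.** 24 practices as 4 sequences of 6 (5.1: "with 4 clusters of 6 practices each switching from control to intervention every 3 months"); about 1300 patients per practice; ICC 0.05; baseline 30%; gain 10 points; α 0.05 (10.2).

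Assumptions made here: two-sided test, five periods with categorical time, cluster j read as practice, percentage-point scale as in the displayed model, and variance taken at the mid-rate of 35%.

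**1. The plan's own figure (same gain everywhere).**
- Total variance: 0.35 × 0.65 = 0.2275.
- Practice variance: τ² = 0.05 × 0.2275 = 0.011375.
- Variance of a practice-period mean: e² = 0.95 × 0.2275 / 1300 = 0.000166.
- Hussey-Hughes variance: I·e²(e² + Tτ²) / [(IU − W)e² + (U² + ITU − TW − IV)τ²], with I = 24, T = 5, U = 60, W = 1080, V = 180. The bracketed terms are 360 and 1080.
- Var(θ) = 24 × 0.000166 × 0.05704 / (0.0599 + 12.285) = 0.0000184, so SE = 0.43 points.
- Power = Φ(10/0.43 − 1.96), above 99.9%.

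Every AWV cell of Table 4 likewise exceeds 99.9% under these assumptions. The stated figure reproduces.

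**2. Size of the spread.** The pilot's 40% is read as percentage points.

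| Pilot gains | Mean | SD | SD/mean | SD scaled to a 10-point mean |
|---|---|---|---|---|
| 40, 40, 15 | 31.7 | 14.4 | 0.46 | 4.6 |
| 40, 40, 6 | 28.7 | 19.6 | 0.68 | 6.8 |

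The scaled spread is therefore about 5 to 7 points and the unscaled spread about 14 to 20.

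**3. True standard error of the one-θ estimator.** Written as a weighted sum of practice gains, its weights per practice are 0.0337, 0.0500, 0.0498 and 0.0332 in sequences 1 to 4. They sum to 1 over the 24 practices, and their squares sum to 0.0433.
- Target A, the average over practices in general: true SE² = 0.43² + 0.0433 × SD².
- Target B, the average over these 24 practices: true SE² = 0.43² + (0.0433 − 1/24) × SD².
- Coverage = 2Φ(1.96 × 0.43 / true SE) − 1.

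| SD of gains | Model SE | True SE, A | Coverage, A | True SE, B | Coverage, B |
|---|---|---|---|---|---|
| 5 | 0.43 | 1.13 | 55% | 0.48 | 92% |
| 7 | 0.43 | 1.52 | 42% | 0.51 | 90% |
| 14.4 | 0.43 | 3.03 | 22% | 0.72 | 75% |
| 19.6 | 0.43 | 4.11 | 16% | 0.90 | 65% |

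Using 1200 patients, or a variance taken at 30%, moves these coverages by a point or two.

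**4. Power of a model that allows practice-specific gains (AWV only, mean gain 10 points).** Refitting step 1 with a practice-level random treatment effect gives:

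| SD of gains | SE | Power |
|---|---|---|
| up to 7 | up to 1.49 | >99% |
| 10 | 2.09 | 99.8% |
| 11 | 2.29 | 99.2% |
| 14.4 | 2.98 | 92% |
| 19.6 | 4.03 | 70% |

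A simple check with SE = SD/√24 gives 2.95 and 4.01 points for the last two rows, and power of 92% and 70%. With a t reference the powers are about 89–90% and 66–67%. Patient numbers hardly matter: at SD 14.4, 800 patients (ICC 0.05) give 91.7% and 1500 (ICC 0.03) give 92.1%.

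**The case against.** A reader might infer that Table 4 is miscalculated, or that the trial's real power is 70 to 92%. The documents support neither.

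- **Table 4 is right on its inputs**, and its scenarios are the ones it lists.
- **The planned test is not the test in step 4.** The one-θ test rejects with probability Φ((10 − 1.96 × 0.43)/true SE), which is about 99.9% at SD 14.4 and 98.7% at SD 19.6. The null in 10.1 is no difference; if no practice changes, there is no spread and the type I error is not inflated by this.
- **The 70 to 92% joins a spread seen around a mean gain of about 30 points to a mean of 10.** If the spread shrinks in proportion, power stays above 99%. A normal distribution with mean 10 and SD 14.4 to 19.6 would have 24 to 30% of practices losing AWVs, which no pilot practice did.
- **The SD comes from three practices.** The 95% interval for 14.4 runs from about 7.5 to 90 points. The pilot figures are also rounded: 40, 40 and 15 weighted by practice size give 36 points, against an overall rise from 7% to 54%.
- **The 24 practices are not a random sample.** They come from organizations that agreed to take part (6.7). If they alone are the target, the undercoverage at SD 5 to 7 is modest.
- **Section 10.4.2 plans subgroup analyses of effect heterogeneity**, including by practice type, and a statistical analysis plan may refine the model.

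All but the last point stand, and they limit the size of the finding. The last does not remove it. Subgroup terms describe differences between types of practice but do not put the remaining practice-to-practice variation into the standard error of the primary effect. The protocol also does not leave the model open: it writes out the random effects.

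**Conclusion.** The concern holds for the interval. If gains differ between practices, as the protocol expects, the displayed primary model understates the standard error under either target. The shortfall is large for the average over practices in general: 42 to 55% coverage at the favourable, scaled-down spread. For the 24 trial practices it is small at that spread (about 89 to 93%) and material at the unscaled pilot spread (about 65 to 75%).

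For power, the finding is an unstated assumption and not a calculation error. The figures of about 92% and 70% are a conditional illustration.

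These sizes rest on the five-period layout, a gain that is constant after crossover, and an SD from three practices. The pilot gains concern AWVs only, so no figure follows for the composite score.

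**What to change.** **10.4.2.** Add a practice-level random treatment effect to the primary model, replacing θX with (θ + u_j)X, where u_j is normal with mean zero. Alternatively, keep one θ and use a cluster-robust variance by practice with a small-sample correction. Specify this before analysis, so that it is not a choice made after seeing results.

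**10.2.** State that Table 4 assumes the same gain in every practice. Add a sensitivity line for AWV utilization under the model that allows gains to differ: above 99% up to an SD of about 11 points, about 92% at 14 and about 70% at 20. Label it illustrative, because the SD comes from three practices whose mean gain was about 30 points, and imply no figure for the composite score.

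**Cost.** One variance component or variance option and a short paragraph. Intervals become wider and the power statement less favourable. If only these 24 practices were the target, the interval would err on the wide side. No extra practices, patients or data are needed.
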